### Study Design

This study has been registered with Clinical Trials.gov (NCT05879549). It is a 3-arm, parallel-group, single-blinded randomized controlled trial. This trial has been reported according to CONSORT (Consolidated Standards of Reporting Trials) guidelines (Multimedia Appendix 2) and the SPIRIT (Standard Protocol Items: Recommendations for Interventional Trials) checklist (Multimedia Appendix 3). This study will be performed in Istanbul University-Cerrahpaşa Laboratory. A permit has been obtained from the institution. The demographic characteristics of the participants (age, height, weight, diseases, etc) will be recorded. Participants will be divided into 3 groups using a simple randomization method according to the order of arrival (1:1:1) with a web-based randomizer. Participants do not know the exercise group that they will be included in nor will they know the differences between the exercises. The flowchart of this study is shown in Figure 1.

**Figure 1 figure1:**
[figure not shown]
Flowchart in this study.

### Outcome Measures

The primary outcome measures are medio-lateral swing, anterior-posterior swing, walking speed, and Hemophilia Joint Health Score. Secondary outcome measures are kinematic assessment of gait, one-leg stand test, 6-minute walk distance (6MWD), proprioception assessment, and Functional Independence Score in Hemophilia. All patients will have completed their factor replacement 1 hour before the assessment section.

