## Methods

### Participant Selection

The sample size was calculated as 18 individuals for each group using the G*Power program (version 3.1.9.4; Heinrich Heine University) with 90% power and .05 type 1 error using the medio-lateral swing effect size value as reference in the balance assessment in the study by Tat et al [19]. Considering that there might be individuals who would not complete the study, a total of 63 participants, that is, 21 individuals for each group, will be included.

The inclusion criteria of the participants in this study were as follows: (1) diagnosed with hemophilia A and hemophilia B, (2) have a blood factor level below 5%, (3) is 13-25 years of age, (4) have a history of bleeding in the lower extremities, (5) have a target joint, (6) have a total lower extremity Hemophilia Joint Health Score ≥3, and (7) is receiving prophylaxis (factor support to prevent bleeding). The exclusion criteria were as follows: (1) individuals having undergone lower extremity surgery in the last 6 months, (2) having BMI>30 kg/m^2^, (3) having an inhibitor, (4) using a walking aid, and (5) being involved in any physiotherapy or exercise program in the last 6 months.

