#### Postural Sway

Postural sway will be evaluated using the Biodex balance system, which is a reliable method (Figure 2) [20]. Postural sway, center of pressure, center of gravity, anterior-posterior, and lateral sway will be evaluated with eyes closed and open.

Patients will be informed about the purpose and performance of the tests before the assessment. Each test will be repeated 3 times. A lower sway index in all tests indicates a better postural stability, while an increase in the sway index indicates a decrease in postural stability (Figure 3).

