### Statistical Analysis

Data will be statically analyzed using SPSS (version 25.0; IBM Corp). Normality tests (visual and analytical) will be applied. Descriptive statistics will be presented as mean (SD) or frequency (percentage). The Shapiro-Wilk test will be used to assess the normality of data distribution. For normally distributed data, a one-way analysis of variance test will be applied for between-group comparisons, and a 2-sided paired sample *t* test will be used for within-group changes. For nonnormally distributed data, the Kruskal-Wallis test will be used for between-group comparisons, and the Wilcoxon test will be applied for within-group changes. In cases where between-group comparisons of normally distributed data show significant results, Tukey or Bonferroni corrections will be used as post hoc analyses to identify the source of the differences. For nonnormalized distributed data, Mann-Whitney *U* tests will be conducted for between-group comparisons. A *P* value <.05 will be considered statistically significant for all analyses.

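### Four primary outcomes are each tested at P<.05 with no control across them, while the .05 error rate and 90% power were set for medio-lateral sway alone

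*Protocol article*

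**What the plan says.** - **Primary outcomes.** The protocol article, Outcome Measures, says: "The primary outcome measures are medio-lateral swing, anterior-posterior swing, walking speed, and Hemophilia Joint Health Score". The Abstract gives the same list. Neither gives an order, a rule for combining the four, or a split of alpha.
- **Threshold.** Statistical Analysis ends with a P "value <.05 will be considered statistically significant for all analyses". The between-group test for each outcome is a one-way ANOVA over three arms, or Kruskal-Wallis if the data are not normal.
- **Correction.** The only one named is Tukey or Bonferroni, used after a significant between-group result in normally distributed data to locate the difference between arms. For non-normal data, Mann-Whitney tests are named with no correction.
- **Sample size.** Participant Selection says: "The sample size was calculated as 18 individuals for each group using the G*Power program", "with 90% power and .05 type 1 error using the medio-lateral swing effect size value as reference in the balance assessment". After an allowance for dropout, "a total of 63 participants, that is, 21 individuals for each group, will be included".
- **Eye conditions.** Under Postural Sway, anterior-posterior and "lateral sway will be evaluated with eyes closed and open". The article does not say which condition supplies the primary sway values.

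**The concern.** The design calculation promises a 5% false-positive risk and 90% power, but for one outcome. Three more outcomes carry the same primary label and are tested at the same threshold. Tukey or Bonferroni across pairs of arms protects against multiple comparisons within an outcome and does nothing across outcomes. Under the analysis as written, the chance that some primary outcome is significant when neither exercise programme works is well above .05. The Discussion intends the comparison to inform the choice of exercise programmes for people with hemophilia, so a chance finding on one primary outcome could be read as evidence for a programme.

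**Working it through.** **Inputs from the article.** Four primary outcomes (Outcome Measures); threshold .05 for each and one three-arm omnibus test per outcome (Statistical Analysis); 18 evaluable per arm, 21 recruited per arm, 90% power, alpha .05, based on medio-lateral sway (Participant Selection).

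**Assumed.** The correlations among the four outcomes are not given. A common correlation from 0 to 0.9 is examined.

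**1. The plan's own figure.** The effect size is not stated as a number, so 18 per arm cannot be reproduced forward. Solving backwards with the noncentral F distribution (3 arms, 18 per arm, alpha .05, power .90) gives Cohen's f of about 0.50. The allowance is consistent: 18/21 = 0.857, an implied dropout of 14.3%, and 3 × 21 = 63. Nothing here shows the sample size to be wrong. It simply belongs to one outcome.

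**2. Error rate for four independent tests.**

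1 − (1 − 0.05)^4 = 1 − 0.8145 = 0.1855, or 18.5%.

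**3. Error rate for correlated tests.** Simulation of four normal outcomes in 3 arms of 18, no true effect, one ANOVA per outcome at .05, 60,000 trials per setting:

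| Assumed common correlation | Chance of at least one P<.05 |
|---|---|
| 0.3 | 17.6% |
| 0.5 | 15.8% |
| 0.7 | 13.3% |
| 0.9 | 9.7% |

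With unequal correlations the picture is similar. If the two sway measures correlate at 0.7 and all other pairs at 0.3, the figure is 16.8%; at 0.8 and 0.5 it is 15.0%.

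**4. If both eye conditions were tested separately.** Two sway outcomes × 2 conditions + walking speed + Hemophilia Joint Health Score = 6 tests. If independent, 1 − 0.95^6 = 0.265, or 26.5%. At a common correlation of 0.5 it is about 21%.

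**5. What adjustment across four would cost.** Holm's first step uses 0.05/4 = 0.0125. At f of about 0.50, power at 0.0125 is 76% with 18 per arm and 84% with 21 per arm, against the planned 90%. Holding 90% at 0.0125 needs 24 evaluable per arm. With the same allowance, 24/0.857 = 28 per arm, or 84 in total.

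**The case against.** **A fuller analysis plan may handle multiplicity.** An article condenses, and silence on this would be no finding. The .05 sentence also covers the post hoc tests, where it must refer to adjusted P values, so it does not strictly exclude adjustment across outcomes. That is fair as far as it goes. But the article is not silent: it fixes .05 for all analyses, names the corrections it will use, and confines them to arms within an outcome. Read as written, the four primary tests are unadjusted.

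**The size depends on correlations nobody has stated.** This stands. A reader might infer a firm 15% to 19% risk, but the lower end of that range holds only if correlations stay below about 0.6. Both sway measures come from the same Biodex assessment and could correlate strongly. What survives is the direction: even at a common correlation of 0.9 the risk is about twice the nominal 5%.

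**Six tests are not planned.** This also stands. A reader might infer from Postural Sway that the four outcomes are really at least six primary tests. That section describes measurement only; one condition could be chosen or the two combined. Six is an upper case for one test per sway outcome and eye condition, left open because the primary condition is not named.

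**The article never says one significant outcome makes the trial positive.** Correct. The aim is framed as studying effects on several parameters. Claiming success on whichever outcome crosses .05 is something the text permits, not something it announces.

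**Conclusion.** The concern holds. The .05 type 1 error in Participant Selection does not describe the primary family as the article sets it up. The chance of at least one false-positive between-group primary result is 18.5% under independence and about 18%, 16%, 13% and 10% at assumed common correlations of 0.3, 0.5, 0.7 and 0.9. These figures assume no effect on any outcome, normal data, 18 per arm and exactly one omnibus test per outcome. They are not a ceiling: testing both eye conditions, or treating the within-group tests as evidence of benefit, would raise them. Testing both eye conditions separately would give up to 26.5%, but the article does not state that plan. Because the primary claim is affected and analysis has not begun, this should be settled before any outcome is compared between arms.

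**What to change.** **Preferred.** Name medio-lateral sway, in one stated eye condition and with a stated summary of the three repetitions, as the single primary outcome. Test anterior-posterior sway, walking speed and Hemophilia Joint Health Score as key secondary outcomes, in a fixed order or by Holm. The choice follows the protocol's own sample-size basis, so it does not depend on results. It keeps alpha at .05, the planned 90% power and N=63, and needs no new data.

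Its cost is real. The stated aim covers balance and walking, and gait and joint health would leave the primary question. It is also a late change: by April 2025, 34 participants had completed treatment. It must be made before analysis and without sight of results by arm, and reported with its date and reason. The registry entry, which was not available for this review, should be checked and brought into line.

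**Alternative.** Keep all four as primary, apply Holm across the four omnibus tests at an overall .05, and name one eye condition for each sway outcome. Restate the power: at the back-solved effect, the first Holm step gives about 76% with 18 evaluable per arm, or 84% if all 21 are evaluable. Restoring 90% at that step would need about 84 participants instead of 63.

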#### Postural Sway

Postural sway will be evaluated using the Biodex balance system, which is a reliable method (Figure 2) [20]. Postural sway, center of pressure, center of gravity, anterior-posterior, and lateral sway will be evaluated with eyes closed and open.

Patients will be informed about the purpose and performance of the tests before the assessment. Each test will be repeated 3 times. A lower sway index in all tests indicates a better postural stability, while an increase in the sway index indicates a decrease in postural stability (Figure 3).

**Figure 2 figure2:**
[figure not shown]
Biodex balance system.

**Figure 3 figure3:**
[figure not shown]
Example of postural sway. (A) Postural sway with eyes open. (B) Postural sway with eyes closed.

#### Joint Health

The Hemophilia Joint Health Score is a hemophilia-specific score, including measurements of muscle strength; edema; crepitation; range of motion of bilateral elbow, knee, and ankle joints; and assessments related to walking [21]. The maximum score to be obtained from each joint is 20, and the maximum score to be obtained from the global gait score is 4. The maximum score to be obtained from the assessment tool is calculated as 124, and a high score indicates poor joint health. The parameters to be evaluated within the scope of the score are as follows: swelling, swelling duration, muscle atrophy, flexion and extension loss, joint pain, muscle strength, and global gait score.

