**Methods:**

This study is a 3-arm, parallel-group randomized controlled trial with 63 people with hemophilia aged 13-25 years who meet the inclusion criteria. The primary outcome measures are medio-lateral swing, anterior-posterior swing, walking speed, and Hemophilia Joint Health Score. Secondary outcome measures are kinematic assessment of gait, one-leg stand test, 6-minute walk distance (6MWD) test, proprioception assessment, and the Functional Independence Score in Hemophilia. Participants will be evaluated with the Biodex balance system for postural sway, 10-meters walking test for gait speed, Hemophilia Joint Health Score for joint health, Kinovea 2D motion analysis for kinematic evaluation of gait, one-leg stand test for balance measurement, 6MWD for functional capacity, digital goniometer for proprioception, and Functional Independence Score in Hemophilia for functional independence. Participants will be randomly assigned to a closed kinetic chain exercise group, a proprioceptive exercise group, or a control group. All participants in exercise training groups will receive a 30-minute education session on joint protection techniques and energy conservation prior to the first exercise session. Closed kinetic chain exercises will include progressive lower limb exercises of approximately 45 minutes each session. Proprioceptive exercise training will focus on vibration training; reposition exercises and proprioception exercises will be administered to increase proprioceptive input for the same duration as the other group. The control group will receive no intervention. All participants will undergo 24 exercise sessions (2 days a week for 12 weeks). After the treatment, the initial measurements will be repeated.

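### The HJHS primary outcome reads as the 0–124 total with both elbows, although training is essentially lower-limb and a lower-extremity score is already used for entry

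*Protocol article*

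**What the plan says.** Outcome Measures lists the score without qualification: "The primary outcome measures are medio-lateral swing, anterior-posterior swing, walking speed, and Hemophilia Joint Health Score". The Abstract does the same.

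The only description of the score is in Joint Health. It covers "range of motion of bilateral elbow, knee, and ankle joints", with the scoring given as "The maximum score to be obtained from each joint is 20, and the maximum score to be obtained from the global gait score is 4" and the ceiling as "The maximum score to be obtained from the assessment tool is calculated as 124".

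Participant Selection uses a different quantity for entry. Participants must "have a total lower extremity Hemophilia Joint Health Score ≥3".

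On training content, the Abstract states "Closed kinetic chain exercises will include progressive lower limb exercises", and Table 1 of the article bears this out. The proprioceptive programme (its own section and Table 2) consists of vibration at the knee and ankle, foot repositioning, and standing or walking balance tasks. Upper-limb content is limited to shoulder circles and elbow stretching in a five-minute warm-up shared by both exercise arms, and to one education session on joint protection that includes lifting technique and care of the hands.

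Statistical Analysis plans a one-way ANOVA between groups (Kruskal-Wallis if nonnormal). It mentions no baseline adjustment.

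**The concern.** The objective is balance and walking, and the trained joints are in the legs. A score that includes the elbows therefore carries a component that the programmes have little means of changing. The Introduction names the elbow among the three joints most often affected in hemophilia, and no exclusion criterion removes elbow disease. The entry requirement of a target joint is not confined to the leg. Elbow scores may therefore differ between participants, and an elbow bleed or recovery over the 12 weeks could move a primary outcome for reasons unrelated to the training.

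At stake is precision on one of four primary outcomes. Adding a non-responding component does not bias the mean difference in points. It widens the spread around that difference, so a real lower-limb benefit is harder to detect.

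**Working it through.** **Inputs from the article.** Six joints at 20 points each and gait at 4 (Joint Health); three groups, 18 per group, 90% power, type 1 error .05, sized on medio-lateral swing (Participant Selection); one-way ANOVA (Statistical Analysis). The article gives no effect size or SD for HJHS and does not print the medio-lateral effect size.

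**Step 1: the scale.** 6 × 20 + 4 = 124, which reproduces the stated maximum. Elbows: 2 × 20 = 40, and 40/124 = 32.3%. Lower-limb version (two knees, two ankles, gait): 4 × 20 + 4 = 84.

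**Step 2: a reference effect.** For a three-group ANOVA with 18 per group (F on 2 and 51 degrees of freedom, α = .05), 90% power corresponds to Cohen's f = 0.499, a noncentrality of 54 × 0.499² ≈ 13.4. This is back-solved, because 18 cannot be reproduced from printed inputs. Applying f ≈ 0.50 to the lower-limb HJHS is an assumption made only to show scale.

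**Step 3: dilution.** Let r be the elbow SD divided by the lower-limb SD of whatever quantity is analysed, and ρ their correlation. If the elbows do not respond, the raw difference is unchanged and the SD is multiplied by √(1 + r² + 2ρr). The standardised effect is therefore multiplied by

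1 / √(1 + r² + 2ρr).

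Example, r = 0.5 and ρ = 0: 1/√1.25 = 0.894, so f becomes 0.499 × 0.894 = 0.446.

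**Step 4: power from the noncentral F.**

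| r | Factor, ρ = 0 | Power, 18 per group | Power, 21 per group | Factor, ρ = 0.5 | Power, 18 per group |
|---|---|---|---|---|---|
| 0 | 1.00 | 90% | 94% | 1.00 | 90% |
| 0.25 | 0.97 | 88% | 93% | 0.87 | 80% |
| 0.5 | 0.89 | 82% | 88% | 0.76 | 67% |
| 0.75 | 0.80 | 72% | 80% | 0.66 | 54% |
| 1 | 0.71 | 61% | 69% | 0.58 | 44% |

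The 21-per-group column is the planned enrolment with no dropout, at ρ = 0. Positive correlation makes the loss larger. A correlation below −r/2 would remove or reverse it.

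The value of r depends on the analysed quantity. If raw post-treatment scores are compared, long-standing elbow damage counts towards r. With change scores or baseline adjustment, stable damage largely drops out and r shrinks.

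**The case against.** The strongest reply is that Joint Health describes an instrument, not an analysis variable. No sentence says that the 124-point total will be compared between groups, and a condensed article may leave that choice to a fuller document. A reader might infer that the outcome is fixed on the total; the text does not go that far. What stands is that the article writes lower extremity when it means the leg score, as in the entry criterion, and writes the name unqualified for the outcome. The total is therefore the natural reading, but it remains an inference.

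Second, the elbows may not be wholly without a treatment effect. The warm-up and the education session reach the exercise arms and not the control arm. That is fair, but the content is brief and has no stated progression, so a material elbow effect is not what the trial is built to produce.

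Third, elbow scores may hardly vary. Participants are selected for lower-limb bleeding and lower-limb joint damage, all receive prophylaxis, and those with inhibitors are excluded. This objection stands in full as to size: nothing in the article separates a negligible loss from a material one.

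Fourth, using a complete validated-type instrument for joint health is defensible, and an entry threshold and an outcome may properly use different scores. There is no contradiction between the two sections, and none is claimed here.

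**Conclusion.** The point holds as a matter of outcome choice and precision. The joint-health primary outcome, as described, most naturally includes 40 of 124 points from joints that the programmes essentially do not train, while a better-matched score is already computed for entry. If elbow scores vary and do not respond, the point difference is unaffected but the standardised effect and power fall.

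The size rests on assumed values of r and ρ and on f ≈ 0.50 for the lower-limb score. At 18 per group and ρ = 0 it runs from nothing (r near 0) or 88% against 90% (r = 0.25) to 82% (r = 0.5) and 72% (r = 0.75).

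Two stronger readings are not supported:

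- A reader might take the elbows' 32% of the points as 32% of the variance and conclude that the trial needs 1/(1 − 0.32) = 1.47 times the sample. Maximum points do not determine variance, and the article gives no HJHS variances.
- A reader might conclude that the 18 or 21 per group is wrong. Those figures were derived for medio-lateral swing, and the article reports no power calculation for HJHS, so no stated figure is affected.

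**What to change.** Before analysis starts, by a dated and justified amendment:

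- name the lower-extremity HJHS (both knees, both ankles and global gait, 0–84) as the joint-health primary outcome;
- compare the groups with adjustment for the baseline value of that score, in place of an unadjusted one-way ANOVA;
- report the 0–124 total alongside as a secondary outcome.

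No new data are needed: the instrument is scored joint by joint, and the initial measurements are repeated after treatment.

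The costs are real but modest. The change comes late: the Results section reports 34 participants through treatment by April 2025 and completion expected in May 2025. Changing a primary outcome of a registered trial at that stage must be disclosed. The same section says analysis begins only after all enrolled participants finish, which leaves room to fix the definition beforehand. The main joint-health figure becomes less directly comparable with studies that report the total. The primary score would also be essentially the one thresholded at entry, which makes regression to the mean more prominent in the planned within-group tests; conclusions should rest on the between-group comparison.

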#### Kinematic Evaluation of Gait

The spatiotemporal parameters of hip, knee, and ankle joints and walking speed will be analyzed during walking using Kinovea 2D motion analysis software (Figure 4). In order to evaluate the lower extremity joint angles during walking, video footages will be taken with 2 cameras fixed with a tripod placed laterally and anteriorly [22]. The fifth metatarsophalangeal joint, lateral malleolus, lateral femoral condyle, and trochanter major will be marked using the reflector tape (adhesive circular tapes that contrast with the background).

